## Abstract

**Background:**

Participation in regular physical activity (PA) during the early years helps children achieve healthy body weight and can substantially improve motor development, bone health, psychosocial health and cognitive development. Despite common assumptions that young children are naturally active, evidence shows that they are insufficiently active for health and developmental benefits. Exploring strategies to increase physical activity in young children is a public health and research priority.

**Methods:**

*Jump Start* is a multi-component, multi-setting PA and gross motor skill intervention for young children aged 3–5 years in disadvantaged areas of New South Wales, Australia. The intervention will be evaluated using a two-arm, parallel group, randomised cluster trial. The *Jump Start* protocol was based on Social Cognitive Theory and includes five components: a structured gross motor skill lesson (Jump In); unstructured outdoor PA and gross motor skill time (Jump Out); energy breaks (Jump Up); activities connecting movement to learning experiences (Jump Through); and a home-based family component to promote PA and gross motor skill (Jump Home). Early childhood education and care centres will be demographically matched and randomised to *Jump Start* (intervention) or usual practice (comparison) group. The intervention group receive *Jump Start* professional development, program resources, monthly newsletters and ongoing intervention support. Outcomes include change in total PA (accelerometers) within centre hours, gross motor skill development (Test of Gross Motor Development-2), weight status (body mass index), bone strength (Sunlight MiniOmni Ultrasound Bone Sonometer), self-regulation (Heads-Toes-Knees-Shoulders, executive function tasks, and proxy-report Temperament and Approaches to learning scales), and educator and parent self-efficacy. Extensive quantitative and qualitative process evaluation and a cost-effectiveness evaluation will be conducted.

**Discussion:**

The *Jump Start* intervention is a unique program to address low levels of PA and gross motor skill proficiency, and support healthy lifestyle behaviours among young children in disadvantaged communities. If shown to be efficacious, the *Jump Start* approach can be expected to have implications for early childhood education and care policies and practices, and ultimately a positive effect on the health and development across the life course.

**Trial registration:**

Australian and New Zealand Clinical Trials Registry No: ACTRN12614000597695, first received: June 5, 2014.

## Background

The early years (defined here as the first five years of life) are a critical time for the development of lifetime healthy behaviours, including physical activity [1, 2]. Regular participation in light physical activity (LPA) and moderate- to vigorous physical activity (MVPA) during the early years has been shown to help young children maintain a healthy body weight, as well as substantially improve motor development, bone health, psychosocial health and cognitive development [2]. Recently, a number of countries, including Canada [3], United States [4], United Kingdom [5] and Australia [6], have developed activity guidelines specifically for children under the age of five years, with most recommending that children should engage in at least 180 min in any activity daily, including both LPA and MVPA, for general health and developmental outcomes [3, 5, 6]. International studies have reported variations in the percentage of young children meeting these guidelines, with approximately 5 % of Australian young children, 84 % of Canadian young children and 100 % of UK children meeting these guidelines. Variation in the estimates of daily physical activity can partly be attributed to differences in measurement and data processing protocols, and sampling differences [7, 8]. Despite these international variations, there is still a consensus for a need to explore strategies to increase and maintain the number of young children who are sufficiently active for health benefits [1, 9–11].

Recent evidence is emerging to show that engagement in physical activity during the early years has critical health and developmental implications that can persist across the life course. It has been shown that engaging in physical activity stimulates neurocognitive processes and promotes children’s capacity to regulate their behavioural actions [12, 13]. In addition, motor skill development has been shown to be a consistent correlate of physical activity [14, 15] and motor skill proficiency can open up opportunities to be active across a range of settings during the early years [16]. A recent systematic review has also shown the benefits of physical activity on weight status with four out of seven studies showing that children who were more active at age 5, had smaller gains in adiposity over time [2]. Engaging in at least 30 min of MVPA a day at age 5 can significantly increase children’s bone strength at ages 8 and 11 [17]. Given the small but growing body of current scientific evidence of the health benefits of physical activity for young children, promotion of physical activity during the early years needs to be a research priority [18].

Recent attention has focused on Early Childhood Education and Care (ECEC) settings as potential locations for reaching and delivering physical activity interventions for promotion of health and developmental outcomes, particularly those serving families in disadvantaged areas [19]. In a recent report from the Organisation for Economic Co-operation and Development (OECD), almost all OECD countries have adopted quality curriculum standards and frameworks for children aged three years and up [20]. These quality standards and frameworks highlight the need to provide physical activity opportunities for children while they are attending ECEC settings [20]. Despite these quality requirements, children accumulate relatively little physical activity in ECEC settings with children spending on average between 6.2 to 15 % of their ECEC day engaged in physical activity [21, 22], which is well below the recommended 25 % [23–26]. A number of studies have shown that lack of sufficient training in physical activity promotion among early childhood educators, a poor balance between structured and unstructured activity, a lack of equipment and resources and limited or no physical activity practices and policies may be contributing to the low activity levels of children at ECEC centres [1, 27–31].

To date, there is limited evidence of the effectiveness of interventions aimed at increasing physical activity levels of young children in ECEC settings [16, 32]. A recent systematic review conducted by Ward et al. [1] identified 19 studies which reported physical activity interventions in ECEC settings with varied levels of effectiveness. Through the evaluation of these studies, Ward et al. [1] provided recommendations for future ECEC-based interventions, including using a formal curriculum on a regular basis to implement structured physical activity, providing a balance between structured and unstructured physical activity opportunities (such as free or self-directed play), providing sufficient amounts of equipment, and providing regular training for educators in how to provide structured physical activity (particularly around integrating physical activity into the academic curriculum). Due to the infancy of ECEC-based physical activity intervention research, there is a need for additional evidence and evaluation of potential effective strategies in these settings. Therefore, this paper provides a description of the protocols and rationale for the *Jump Start* intervention, a randomised controlled trial implemented in ECEC settings in Australia.

The primary hypothesis is that at post-intervention (18-months), children in ECEC centres allocated to the *Jump Start* intervention will significantly increase total physical activity (i.e. light, moderate, and vigorous intensity physical activity (LMVPA)) while at the ECEC centre compared to children in centres allocated to the usual practice comparison group. The secondary aims are to: (1) examine the relative effects of the intervention on other health and developmental outcomes, including MVPA, sedentary time, self-regulation, weight status, bone strength, and gross motor skills; and (2) explore the potential mediating and moderating variables, cost-effectiveness and implications for public policy decision making.

## Methods

### Study design

The *Jump Start* study is a two-arm, parallel group, cluster randomised controlled trial (RCT) using a nested-cohort design [33] (Fig. 1). The development of the *Jump Start* intervention was informed by formative research, involving two ECEC parent organisations and ECEC educators employed by those organisations. The two ECEC parent organisations have collaborated on several of the *Jump Start* pilot studies and provided input into the intervention components and their implementation. Educator professional development and training around physical activity promotion and gross motor development, and focusing on disadvantaged communities were identified by all parties as the highest priorities.

**Fig. 1 Fig1:**
[figure not shown]
CONSORT flowchart

The *Jump Start* intervention has been designed using the recommended framework for developing and evaluating complex interventions [34]. This design enables the assessment of intervention effects at 6- and 18-month follow-up when the children assessed at baseline will still be attending the ECEC centre (i.e., not transitioned to primary school). Assessments took place at baseline (February-June 2015), 6-months (August-December 2015) and will be repeated at 18-months (August–December 2016). The primary outcome is change in total physical activity (LMVPA) while at the ECEC centre over the 18-month study period.

ECEC centres were randomised to either the *Jump Start* intervention or usual practice comparison group. The *Jump Start* intervention is a multi-component, multi-setting approach that combines evidence-based intervention components [28, 30, 31, 35, 36] targeting multiple influences on physical activity among preschoolers (children aged 3–5 years) living in disadvantaged areas of New South Wales (NSW). It consists of five main components: a structured gross motor lesson (Jump In); unstructured outdoor physical activity and gross motor time (Jump Out); energy breaks (Jump Up); activities connecting movement to learning experiences (Jump Through); and a home-based family component to promote physical activity and gross motor development (Jump Home). These components have previously been evaluated independently and have shown high feasibility and potential efficacy across a number of settings [28, 30, 31, 35, 36] but have yet to be tested as a comprehensive approach within ECEC settings.

The trial is being conducted in accordance with Consolidated Standards of Reporting Trials (CONSORT) guidelines for cluster randomised trials [37]. All study procedures have been approved by the University of Wollongong Human Research Ethics Committee (HE14/137) and registered with the Australian and New Zealand Clinical Trials Registry (ACTRN12614000597695).

### Participant recruitment and eligibility criteria

The sampling frame comprised ECEC centres located in areas of disadvantage in NSW, Australia, according to the area location indices for socio-economic disadvantage (SEIFA) [38]. Centres were eligible if they were located in an area with a SEIFA index of relative socioeconomic disadvantage of less than or equal to 5 (lowest 50 %) [38] and had a minimum enrolment of five eligible consenting children. From the 74 eligible ECEC centres, 57 centres were approached and 44 centres were successfully recruited. One centre withdrew from the study due to not having the minimum number of consenting children (*n* = 3).

Children were eligible to participate in the evaluation components of the study if they were 3 years old, or turning 3 before the start of the intervention; attended at least 2 days a week at a participating ECEC centre; and were not likely to be enrolled in primary school the following year. All parents/caregivers of eligible children received a participant information sheet and a URL YouTube link to a recruitment video and were invited to provide written consent to participate. All educators working with 3 year olds in the ECEC centres were also invited to take part in the study and provide written consent to participation. Educators who are employed in centre-based ECEC services across Australia, and who are responsible for a group of children, are required by national regulations to hold at least a 12-month vocational qualification to work with children or be enrolled to complete such a vocational qualification [39]. Recruitment began in January 2015 and was completed in June 2015.

### Power and sample size

Sample size and power estimates were based on the formula proposed by Murray [33] to adjust for a clustered (nested) cohort design. It is recommended that sample size estimates be based on the *a priori* minimum acceptable difference between groups to be considered meaningful [40–42]. Based on our experience and the changes observed in our pilot studies for accelerometer-based physical activity, we estimated this minimum acceptable difference to be 45 mins/day of total physical activity, which translates to an effect size (Cohen’s d) of 0.4. The 6-month Jump Start pilot [14] resulted in a Cohen’s *d* = 0.4 for counts per min, and the 6-month Jump Start translational pilot resulted in a Cohen’s *d* = 0.39 for percentage of time spent in LPA [43]. We therefore concluded that achieving an effect size ≥ 0.4 was realistic and our multi-component intervention strategies, with an increased intervention length and intensity compared to our pilot studies, would be expected to produce an effect size similar to or greater than these studies. For a two-tailed alpha = 0.05 and an intraclass correlation (ICC) of 0.01–0.05 our proposed sample size of 608 participants (304 per group) provides approximately 86 % power to detect an intervention effect of 0.4 or greater for the ICC range proposed.

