#### Primary outcome measure

##### LMVPA while at the ECEC centre

The primary outcome is time spent in total physical activity (LMVPA) while at the ECEC centre as measured by the ActiGraph accelerometer (ActiGraph Corporation, Pensacola, FL), which has established validity and reliability in young children [7, 51, 52]. Children will be asked to wear an accelerometer for 1 week during waking hours, except during water-based activities, at baseline, and at 6- and 18-months. ActiGraph models used in this project will include GT1M, GT3X, and GT3X+, which display high levels of agreement [53]. Collected accelerometer data will be integrated into 15 s epochs during data reduction. After screening for non-wear periods (≥20 min of consecutive ‘0’ counts), participant data will be considered valid at each time point if they accumulate ≥ 3 h of valid wear time during ECEC centre hours on ≥1 ECEC day. These criteria were chosen because: i) 3 h represented 50 % of a typical ECEC day (9 am - 3 pm), and ii) this study is a group RCT and, as such, the aim is to represent LMVPA at the centre level from individual participant samples. Therefore, less stringent inclusion criteria (e.g., ≥ 1 day) is acceptable because these errors may not bias centre-level estimates, and loss of precision may be overcome by increasing sample size. Epochs recording ≥200 counts/15 s will be classified as LMVPA [54].

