## Discussion

This paper presents the study protocols for the *Jump Start* intervention. This 18-month intervention is unique in its approach to supporting the health behaviours of children living in disadvantaged communities, drawing on evidence and lessons learnt from pilot studies [28, 30, 31, 35, 36] and fostering strong collaborative partnerships between the ECEC sector and multi-disciplinary research team. To the authors’ knowledge, *Jump Start* is one of the first interventions that uses a comprehensive multi-component, multi-setting approach to address the low levels of physical activity and gross motor skill proficiency among preschool-aged children in disadvantaged communities [1].

Targeting young children from disadvantaged communities is important because they typically have limited access to physical activity opportunities, and reduced physical activity levels and gross motor skill proficiency [67–69]. Through the *Jump Start* intervention, we expect to increase total physical activity by a minimum of 45 min/day, 20 min of which will be MVPA. We expect that large and meaningful benefits will flow into other areas of health and development, as evidence shows increases of this magnitude are associated with significant declines in adiposity and significant increases in bone health at ages 8 and 11 years [17]. This approach may also improve behavioural self-regulation skills in this age group, which are better predictors of school readiness than IQ or entry-level literacy or numeracy skills [70].

*Jump Start* will also enhance the quality of early childhood education and care at a crucial time in children’s lives when the architecture of the developing brain is most open to the influences of experiences and when health inequality gaps are smallest. Benefits also accrue for parents and educators. *Jump Start* focuses on capacity building and enhancing the knowledge and self-efficacy of all participating ECEC educators in teaching gross motor skills and integrating physical activity into daily routines through targeted professional learning and on-going support.

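### The 45 min/day minimum difference and d = 0.4 imply an SD of 112.5 min/day, which is not credible for in-centre LMVPA; the sample size rests on 0.4 SD, not on 45 minutes

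*Protocol article*

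**What the plan says.** Power and sample size bases the calculation on the smallest difference regarded as meaningful: "we estimated this minimum acceptable difference to be 45 mins/day of total physical activity, which translates to an effect size", namely a Cohen's d of 0.4. It gives no SD. It supports 0.4 as realistic with two pilot effect sizes: 0.4 for counts per minute and 0.39 for the percentage of time in light activity. With a two-sided alpha of 0.05 and an ICC between 0.01 and 0.05, it then states that "our proposed sample size of 608 participants (304 per group) provides approximately 86 % power" for an effect of that size or larger.

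The primary hypothesis (Background), Study design, and the primary outcome section all define total physical activity for the primary outcome as LMVPA at the centre. The outcome section equates 3 h with 50 % "of a typical ECEC day", given as 9 am to 3 pm. The Background reports that "children accumulate relatively little physical activity in ECEC settings with children spending on average between 6.2 to 15" per cent of the day are spent active, against a recommended 25 per cent.

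The Discussion repeats the figure as an expectation: "we expect to increase total physical activity by a minimum of 45 min/day". It adds that 20 of those minutes will be MVPA and rests its claim of wider health benefits on gains of that size.

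**The concern.** A difference in minutes and a standardised effect size are linked only through the SD. Stating both therefore states the SD, even though the article never prints it. If that SD does not fit the outcome, the two figures describe different targets, and the sample size follows only the standardised one.

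What is at stake is interpretation. The article says the sample size should rest on the difference considered meaningful, and names 45 min/day. If 0.4 SD of in-centre LMVPA is really much less than 45 min, a reader of the 18-month result has two incompatible yardsticks, and the Discussion's claims attach to the larger one.

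**Working it through.** **Inputs.** Difference 45 min/day, d = 0.4, 608 children, two-sided alpha 0.05, ICC 0.01-0.05 (Power and sample size). 44 centres recruited, one later withdrawn (Participant recruitment). Centre day 360 min (primary outcome section). Usual activity 6.2-15% of the day (Background).

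**The stated power.** This depends only on d. With 44 centres there are 608/44 = 13.8 children per centre.
- ICC 0.05: design effect 1 + 12.8 × 0.05 = 1.64. SE = sqrt(2 × 1.64/304) = 0.104 SD. Power = Φ(0.4/0.104 − 1.96) = about 97%.
- ICC 0.01: design effect 1.13, power about 99.6%.

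The stated 86% does not reproduce with the recruited centres. The planned number of centres and any allowance for attrition are not given, so I draw no conclusion from that. What matters is that no SD in minutes enters the calculation.

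**Implied SD.** 45/0.4 = 112.5 min/day.

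**What the outcome allows.** Usual activity is 0.062 × 360 = 22.3 min to 0.15 × 360 = 54 min, so the implied SD is about 5 to 2 times the mean. For a quantity between 0 and T with mean μ, the SD cannot exceed sqrt(μ(T − μ)). For a single-peaked distribution with μ up to T/2, the limit comes from a mass at 0 mixed with a uniform on 0 to T, in proportion p = 2μ/T: variance = pT²/3 − μ².

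| Mean, T = 360 | Absolute limit of SD | Single-peaked limit |
|---|---|---|
| 22.3 min (6.2%) | sqrt(22.3 × 337.7) = 86.8 | sqrt(0.124 × 43,200 − 22.3²) = 69.7 |
| 54 min (15%) | sqrt(54 × 306) = 128.5 | sqrt(0.30 × 43,200 − 54²) = 100.2 |
| 90 min (25%) | sqrt(90 × 270) = 155.9 | sqrt(0.50 × 43,200 − 90²) = 116.2 |

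A uniform spread over the whole day has SD 360/sqrt(12) = 103.9 min. At 6.2%, 112.5 exceeds the absolute limit. At 15% it lies below the absolute limit but above both the uniform SD and the single-peaked limit.

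**Size of the 45 min.** Added to 22.3 or 54 min it gives 67.3 or 99 min, that is 18.7% or 27.5% of the day: activity would about triple or nearly double.

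**What d = 0.4 means in minutes.** The article gives no SD, so a range is assumed.

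| Assumed in-centre SD | 0.4 SD | 45 min as d |
|---|---|---|
| 20 min | 8 min | 2.25 |
| 30 min | 12 min | 1.50 |
| 40 min | 16 min | 1.13 |
| 60 min | 24 min | 0.75 |

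Power for a true 45 min stays above 99.9% for every SD up to 80 min: at 80, d = 0.5625 and Φ(0.5625/0.104 − 1.96) = 0.9997.

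**The case against.** The strongest reply is that impossibility is shown only in one corner. The 9 am to 3 pm day is called typical and serves to justify a wear-time rule; it does not cap attendance. At a 6.2% mean the absolute limit is 0.241T, which passes 112.5 once T exceeds about 467 min. The 6.2-15% comes from cited studies whose definition of activity may be narrower than the LMVPA cut-point, and the Background itself warns that estimates vary with measurement. Both points stand. They turn impossible into not credible, but do not rescue the figure: even at the recommended 25% of a 6-hour day, 112.5 is close to the single-peaked limit of 116.2.

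Second, neither the power section nor the Discussion prints in-centre beside the 45 min, there is a home component, and habitual activity is also measured. On a whole-day reading the limits above do not apply. But then the sample size is anchored to a different quantity from the in-centre primary outcome, which also needs correcting.

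Third, 112.5 might be an SD of change. The cross-sectional SD would then be 112.5/sqrt(2(1 − r)): 79.5 min at r = 0 and 112.5 min at r = 0.5. Even 79.5 exceeds the mean activity the article reports.

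Fourth, an unprinted SD in a condensed article is no fault. Agreed; the fault is the stated equivalence. Nor does the article show how 0.4 was derived: the pilots are cited to call it realistic, so it cannot be asserted that they are its source.

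**Conclusion.** The equivalence is wrong as written for the in-centre primary outcome, or else it concerns a different outcome. The trial is sized for 0.4 SD, which is about 8-24 min per centre day if the SD is 20-60 min. That range is an assumption; the implied 112.5 min is plain arithmetic.

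Four stronger readings are tempting but not supported.
- That the two figures can never both hold: strict impossibility needs a mean of about 6.2% and a 6-hour cap.
- That at 15% nearly every child would have to be inactive or active all day: 81% of children at 0 and 19% at about 288 min would also give mean 54 and SD 112.5. That is implausible, but not all-or-nothing.
- That the trial is underpowered: a true 45-min effect would be detected almost surely.
- That any significant result will be called a success: the article states no such rule, and every adequately powered trial can reach significance below its target difference.

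Type I error, the estimand and the analysis model are untouched. The damage is to the stated target and to how the result, and the Discussion's claim, will be read.

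**What to change.** Before the 18-month data are unblinded:

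1. Compute the pooled, arm-blind SD of in-centre LMVPA minutes from the baseline data already collected, and report it.
2. Restate d = 0.4 in minutes per centre day using that SD.
3. State one minimum meaningful difference in the metric and setting of the primary outcome. If 45 min/day was meant as whole-day activity, label it so and remove it as the basis for the in-centre sample size.
4. Say that the 18-month confidence interval will be read against that difference.
5. Bring the 45 min/day expectation in the Discussion, and the benefits tied to it, into line.

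The cost is wording in two sections and one descriptive calculation; no further participants are needed. The price is that the advertised effect will probably look less impressive. The timing matters, because a minimum difference restated after the results are known would carry little weight.
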